**Tiriso ya metsoko e e farologaneng:**

| TOB.1 A ka se sebaka o dirisa mongwe kgotsa mengwe ya metsoko e e latelang (sakarete, seneifi, motsoko o o tlhafoniwang, disigara, le tse dingwe.)? | **Ee** | **Nyaa** |
| --- | --- | --- |
|  | 1 | 2 |

**Fa osa dumalelane’, e ya kwa letlheng le lengwe**

TOB.2 Mo kgweding e e fetileng, ke ga kae o dirisa e mongwe kgotsa go feta ga mefuta ya metsoko e e latelang (cigarettes, snuff, chewing tobacco, cigars, etc.)?

| Gangwe kgotsa gabedi | 1 |
| --- | --- |
| Beke nngwe le nngwe | 2 |
| Go isa go letsatsi ka letsatsi | 3 |
| Letsatsi lengwe le lengwe | 4 |

#### Annex 4: Patients Information Extract Sheet: HIV related information

| **HIV related information** | | | | | | | |
| --- | --- | --- | --- | --- | --- | --- | --- |
| INTERVIEWER: Please record the latest readings from the medical file of the following: | | | | | | | |
| **Date start ART: _______/_______/______________** | | | | | | | |
| **Lab and clinical** | | | | | | | |
| 1. CD4 Count:_____________________cells/mm^3^ | | | | | | | |
| 1. Viral Load:______________________copies/ml | | | | | | | |
| 1. Opportunistic infections:   __________________________________________________________________________________________________  ____________________________________________________________________________________________________________________________________________________________________________________________________________________ | | | | | | | |
| 1. **WHO clinical stage:** 1. [ ] 2. [ ] 3. [ ] 4. [ ] | | | | | |  | |
| 1. **HIV medication** | | |  | | | | |
| **NRTI**   1. Tenofovir (TDF).......... 2. Lamivudine (3TC) ...... 3. Zidovudine (AZT)........ 4. Stavudine (d4T).......... 5. Emtricitabine (FTC).... 6. Other.......................... | | [ ]  [ ]  [ ]  [ ]  [ ]  [ ] | **NNRTI**   1. Efavirenz (stocrin, EFV) …… 2. Nevirapine (NVP)…………… 3. Other………………………… | [ ]  [ ]  [ ] | **Protease inhibitor (PI)**   1. Lopinavir/ritonavir (LPV/r) (Aluvia)……….. 2. Other…………………. | | [ ] [ ] |
| 1. **Medications for HIV-related opportunistic infections:** | | | | | | | |
| a. | Cotrimoxazole (Nucotrim / Bactrim / Cozole / Purbac) | | | [ ] 1. Yes [ ] 2. No | | | |
| b. | TB treatment 1^st^ line (e.g Rifinah, Rifafour, Rifater, Rimstar, Ethatyl) | | | [ ] 1. Yes [ ] 2. No | | | |
| c. | TB treatment 2^nd^ line (e.g. Cycloserine) | | | [ ] 1. Yes [ ] 2. No | | | |
| d. | Acyclovir | | | [ ] 1. Yes [ ] 2. No | | | |
| e. | Fluconazole (Diflucan) | | | [ ] 1. Yes [ ] 2. No | | | |
| f. | Ciprofloxacin | | | [ ] 1. Yes [ ] 2. No | | | |
| g. | Miconazole (Daktarin) | | | [ ] 1. Yes [ ] 2. No | | | |
| h. | Phenoxymethylpenicillin (e.g. Len V.K.) | | | [ ] 1. Yes [ ] 2. No | | | |
| i. | Anti-diarrhoeal (e.g. Loperamide) | | | [ ] 1. Yes [ ] 2. No | | | |
| j. | Other (specify)______________________________________________ | | | [ ] 1. Yes [ ] 2. No | | | |
| 1. **Non-HIV medications:** | | | | | | | |
| a. | Vitamins (incl. Pyridoxine, Thiamine, Folic acid, Biocare Potassium) | | | [ ] 1. Yes [ ] 2. No | | | |
| b. | Immune supplement (e.g. Moducare) | | | [ ] 1. Yes [ ] 2. No | | | |
| c. | Blood pressure treatment (antihypertensive e.g. Methodopa) | | | [ ] 1. Yes [ ] 2. No | | | |
| d. | Anusol (for piles) | | | [ ] 1. Yes [ ] 2. No | | | |
| e. | Diabetes treatment (e.g. Metformin, Dia-care) | | | [ ] 1. Yes [ ] 2. No | | | |
| f. | Anti-inflammatory (e.g. Brufen, Ibuprofen, Inza) | | | [ ] 1. Yes [ ] 2. No | | | |
| g. | Pain-killer (analgesic e.g. Grandpa) | | | [ ] 1. Yes [ ] 2. No | | | |
| h. | Diuretic (e.g. Ridaq) | | | [ ] 1. Yes [ ] 2. No | | | |
| i. | Heart palpitations treatment (e.g. Cocillana) | | | [ ] 1. Yes [ ] 2. No | | | |
| j. | Emollient, skin cream (e.g. Epizone benzoic) | | | [ ] 1. Yes [ ] 2. No | | | |
| k. | Other :  (specify)______________________________________________ | | | [ ] 1. Yes [ ] 2. No | | | |

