#### Objectives:

- - 1. To measure the prevalence of alcohol consumption among HIV positive hospital outpatients;
    2. To describe drinking patterns, health status, quality of life and sexual behavior among HIV positive out-patients, and identify medium risk drinkers needing intervention;
    3. To compare level of alcohol consumption, health status, quality of life, level of adherence to ART and sexual behavior among medium risk drinkers within the previously identified group between pre intervention, 3 months and 12 months after intervention;
    4. To compare **levels of** (a) alcohol consumption, (b) adherence level to ART, (c) quality of life, (d) health status and (e) number of patients with virological and immunological failure, between intervention and control group at 3 and 12 months;
    5. To compare **changes in** (a) alcohol consumption, (b) adherence level to ART, (c) quality of life, (d) health status and (e) number of patients with virological and immunological failure, between intervention and control group at 3 and 12 months.

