#### HIV related information Data Extract Sheet (Annex 4)

A researcher designed patient information extract sheet will be used to record information related to the HIV infection and will include questions about date of first positive HIV test, start date ART, ART regimen and co-infections. The patientfile will be used to obtain additional information. The computerized laboratory data system will be used to obtain the laboratory results. At follow up CD4 cell counts and viral load will be obtained from the computerized laboratory data system. This data extract sheet will be taken at baseline and laboratory and clinical information will be collected at every study visit; at baseline, 3 and 12 months.

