# Data Analysis

*Definition of virological failure:*

We follow the definition used in the national guidelines in which virological failure is defined as a repeat VL ≥ 1000 copies/ml after intense adherence assessment^38^.

*Definition of immunological failure:*

Immunological failure is defined according to the WHO definition. Failure is defined as a fall of CD4 count to pretherapy baseline (or below), *or* a 50% fall from the on-treatment peak value (if known) *or* a persistent CD4 levels below 100 cells/mm^3^.^39^

Means, standard deviations, and percentages will be used for descriptive statistics. T-test for continuous data and chi-square for categorical data will be used to examine differences between groups. Generalized Linear Model Repeated Measures 2 x 3 Analysis of Variance (ANOVA) will be used for comparing observations (alcohol use score) across the three contact periods to demonstrate a treatment intervention x time interaction.Observations with a single follow-up point missing (at either 3 and 12 months) will be imputed with the available follow-up. Data for participants who are lost to follow-up at 3 and 12 months will be imputed using baseline values. SPSS for Windows version 18.0 (SPSS, Inc., Chicago, IL) will be used for calculations.

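### Annex 4 records one undated latest CD4 count and viral load, too little to classify failure as defined or to show that a 3-month value was drawn after randomisation

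*Protocol*

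**What the plan says.** Objectives 4 and 5 of the Protocol compare levels of, and changes in, several outcomes. The last of the five is the "number of patients with virological and immunological failure, between intervention and control group at 3 and 12 months".

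The Data Analysis section defines both kinds of failure by reference to more than one measurement:

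- Virological: "virological failure is defined as a repeat VL ≥ 1000 copies/ml after intense adherence assessment".
- Immunological: "Failure is defined as a fall of CD4 count to pretherapy baseline (or below"), or a halving from the highest count on treatment where that is known, or a count that stays under 100 cells/mm³.

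Annex 4 is the collection form for this information. Its instruction is: "INTERVIEWER: Please record the latest readings from the medical file of the following". It then gives one blank for CD4 count and one for viral load. The only date on the sheet is the field "Date start ART".

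The section describing Annex 4 in the body of the Protocol gives a different source: "At follow up CD4 cell counts and viral load will be obtained from the computerized laboratory data system". It has the sheet completed at baseline, with laboratory and clinical information gathered at baseline, 3 and 12 months.

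**The concern.** The outcome and the form that feeds it do not match. Each failure criterion needs a history or a second value, and the form holds one value of each kind.

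Nothing ties that value to a visit either. If the form is followed as written at 3 months, the latest reading may be the one already entered at baseline, and without specimen dates nobody could tell from the study data. A specimen drawn before randomisation cannot respond to the intervention. Under objective 4 such values pull the 3-month comparison toward no difference. Under objective 5 a re-recorded baseline result gives a change of zero by construction.

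This goes beyond detail that a later analysis plan could supply, because dates and earlier values that were never collected cannot be analysed.

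**Working it through.** **What each criterion needs against what Annex 4 holds**

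| Criterion (Data Analysis) | Needed | On one completed Annex 4 sheet |
| --- | --- | --- |
| Virological failure | A first high viral load, an adherence assessment, then a repeat load | One viral load, undated |
| CD4 back to the pre-therapy level | Pre-therapy CD4 and current CD4 | One CD4, undated |
| CD4 halved from peak | On-treatment peak (if known) and current CD4 | One CD4, undated |
| Persistently low CD4 | At least two dated CD4 counts | One CD4, undated |

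One sheet on its own establishes none of the four.

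**Source and timing.** Annex 4 points to the medical file. The section describing it points to the laboratory system for follow-up values. Neither sets a window around the visit or asks that the specimen postdate randomisation. No section shown schedules a study blood draw, and the Budget has no laboratory line. The Procedure section calls 3 and 12 months standard HIV-care visit intervals but does not say that CD4 or viral load is measured then.

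**How often could a latest value predate randomisation?** The Protocol gives no figure for this, so there is none to reproduce. Its sample size of 251 per group concerns adherence and plays no part.

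Inputs:

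- t = 3 or 12 months, from the Design section.
- T = months between routine tests. This is not in the document and is an assumption, shown as a range.
- Tests are evenly spaced, and randomisation falls at a random point in the testing cycle (also an assumption).

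At the visit, the age of the latest result is then spread evenly between 0 and T months. It predates randomisation when that age exceeds t:

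share = max(0, 1 − t/T)

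| T (months) | Share at 3 months | Share at 12 months |
| --- | --- | --- |
| 3 | 1 − 3/3 = 0% | 0% |
| 4 | 1 − 3/4 = 25% | 0% |
| 6 | 1 − 3/6 = 50% | 0% |
| 9 | 1 − 3/9 = 67% | 0% |
| 12 | 1 − 3/12 = 75% | 1 − 12/12 = 0% |
| 18 | 1 − 3/18 = 83% | 1 − 12/18 = 33% |

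**Two loads within 3 months.** Two tests T months apart can both fall in the first 3 months only if T is under 3. At a spacing of 3 months or more, essentially no patient has two routine post-randomisation loads by month 3. A repeat load lying wholly after randomisation would need an extra test.

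**The case against.** The strongest reply is that the body of the Protocol, not a form instruction, governs follow-up. It names the laboratory system, collects results on three occasions, and allows the patient file to be used for additional information. A laboratory system may well hold dates and history. Across three visits a second high load or a persistently low CD4 could be seen, and the peak is needed only where known. Annex 4 may also not be the full extraction list: the section describing it mentions the date of the first positive HIV test, which the sheet as shown lacks.

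Much of this stands, and it rules out several stronger readings that a reader might infer:

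- *That 3-month failure is definitely read from an undated file value.* That applies the Annex 4 wording to a visit for which the body names another source. What the documents show is a conflict between the two.
- *That the definitions cannot be met at all.* This is true of one sheet, not of three visits combined or of a laboratory history.
- *That the trial draws no blood.* No section says so. It would be an inference from silence, and some pages were removed from the text available for review.
- *That failures present at baseline are counted as follow-up failures.* The Protocol does not say how they are handled, and objective 5 compares changes.
- *That the 3-month effect shrinks by exactly the shares above.* That would require any post-randomisation specimen, even one drawn within days, to carry the full 3-month effect.

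The reply does not remove the mismatch. The body also sets no window, asks for no specimen date, and does not say that visits will be combined or history retrieved.

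**Conclusion.** The point holds as a mismatch between outcome and data collection. The form lacks specimen dates and the values that the failure definitions need, the two stated sources disagree, and nothing requires a follow-up result to postdate randomisation.

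The risk that a value predates randomisation is mainly a 3-month problem. On the even-spacing assumption the share runs from 0% with 3-monthly tests to 75% with yearly tests, so the range starts at zero and the true figure is unknown. At 12 months it is 0% for any interval up to 12 months. The direction at 3 months is toward no difference, but the size of the dilution cannot be derived from the document. The missing history fields matter at both visits.

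The consequence is confined to the failure outcomes. The sample size rests on adherence and the named repeated-measures model on the alcohol score, and neither is touched. A reader might conclude that the 3-month failure comparison has to go. The documents do not support that, since dated results would show which 3-month values are usable.

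**What to change.** 1. Reconcile Annex 4 with the section that describes it, so that one source is named for CD4 and viral load at each visit.
2. From the laboratory system already in use, extract every CD4 and viral-load result with its specimen date, from before therapy to the 12-month visit.
3. At each visit, classify failure only when the qualifying specimen was drawn after randomisation, and state for each criterion which specimen is the qualifying one.
4. Identify failures already present at baseline so that they are not counted as new.
5. Report, by arm, how many patients have a usable post-randomisation value at 3 months, and treat 12 months as the main failure comparison.

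Restricting the analysis to patients on ART is a separate choice and is not needed here. If ART status were judged at follow-up, the restriction would condition on something that can change after randomisation.

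The cost is a date column, a longer data pull and fewer evaluable patients at 3 months.

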#### Annex 5. Assessment of adherence to ART (compiled by the Pharmacy assistant)

###### Visual Analog Scale (VAS)

| **VAS adherence measure** | |
| --- | --- |
| Most patients find it difficult to take all their HIV medications exactly as prescribed. | |
| 1 How many doses of your HIV medication did you miss in the last 7 days? | _____________________________ (# of doses) |
| 2 Please put a mark on the line below at the point that shows your best guess about how much of your prescribed HIV medication you have  taken in the last month.  Examples: 0% means you have taken no medication  50% means you have taken half your medication  100% means you have taken every single dose of your medication  Visual Analogue Scale 0 10 20 30 40 50 60 70 80 90 100 | |

Patient self report:

###### Pill count

#### Annex 6: Health education leaflet

**LETLAKALA LA THUTO YA TSA BOITEKANELO: Ke eng se se isang kelo ya nnotagi kwa godimo?**

Go nwa nno-agi go fetisa selekano go ka baka tse di latelang:

*Mathata a go ka laola maikutlo*

*Mathata a le kamano le batho ba o tshelang le bone*

*Mathata a mala a botlhoko*

*Letshololo*

*Go tlhoka boroko bosigo*

*Go wela fa fatshe kana dikotsi tse dingwe*

*Go tshwarwa ke mapodisi ka ntlha ya go nwa nno-tagi go feta selekano*

*Mathata a go tlhoka madi (tshelete)*

*Go kopana tlhogo morago ga go nwa nno-tagi*

*Bolwetse jwa maikutlo*

*Go latlhegelwa ke mogopolo*

*Mathata le go nwa melemo ee fodisang*

*Dikotsi tsa sejanaga*

*Go ikutlwa o le nosi ka ntlha ya nnotagi*

*Kelo ya madi e e kwa godimo*

*Go roroma ga diatla*

*Fa mmele o tlhoka dikotla tse di maleba*

*Bolwetse jwa go wa*

*Bolwetse jwa kankere*

*Bolwetse jwa go swa letlhakore kana seterouko*

*Go nwa nnotagi go go feteletseng go ka tlisa pholo e e kwa tlase kgotsa go fetoga ga mekgwa le dikamano tsa gago. O ka tswa o nnile le maiphitlhelo a tse dingwe tsa mathata ao re buileng ka ona fa godimo a tsamaisanang le go nwa nnotagi.*

**Gopola seno:**

Go nwa nno-tagi mo selekanong ke go go latelang:

**Bomme:**

- Se nwe go feta dinnotagi tse pedi fela ka letsatsi.
- Se nwe go feta matsatsi a le mabedi mo bekeng.

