# Interventions

#### Experimental arm:

###### Brief intervention

Participants who are randomized in the intervention arm receive personalized feedback on their AUDIT results, a health education leaflet (Annex 6), plus brief counselling about reducing excessive drinking, during a one session 20 minute intervention.

The steps of brief counselling are: 1) Identify any alcohol related problems mentioned in the interview, 2) Introduce the sensible drinking leaflet, and emphasise the idea of sensible limits, and make sure that patients realize that they are in the medium-risk drinking category, 3) Work through the first 3 sections of the problem solving manual while mentioning the value of reviewing the other sections, 4) Describe drinking diary cards 5) Identify a helper, and 6) mention the 3, 6 and 12 months follow-up. The brief intervention will be based on the WHO brief intervention package for hazardous and harmful drinking^36^. The Information-Motivation-Behavioural Skills (IMB) Model

will be used to guide the alcohol reduction intervention in South Africa.

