**Borre:**

- Se nwe go feta dinno-tagi tse tharo ka letsatsi.
- Se nwe go feta matsatsi a le mabedi mo bekeng.

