**Batho botlhe ba ba leng mo godimo ga dingwaga di le 65**

- Se nwe go feta dinno- tagi tse pedi fela ka letsatsi.
- Se new go feta matsatsi a le mabedi mo bekeng.

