**Appendix 1: Health Education Leaflet English**

HEALTH EDUCATION LEAFLET: What constitutes risky drinking?

Excessive drinking can result in:

Difficulty coping with stress

Relationship problems

Stomach problems

Diarrhoea

Sleeplessness

Falls or other accidents

Arrest for drinking under the influence of alcohol

Financial problems

Feeling confused after drinking

Depression

Memory loss

Problems with medications

Automobile accidents

Feeling alone or left out because of drinking

High blood pressure

Trembling hands

Malnutrition

Seizures

Cancer

Stroke

Drinking too much alcohol can hurt your health, your behaviours, and your relationships. You may have experienced some of the problems shown at the left, which may be related to your use of alcohol.

Remember:

Sensible drinking are:

Women:

- No more than 2 drinks per day
- Do not drink at least 2 days a week

Men:

- No more than 3 drinks per day
- Do not drink at least 2 days a week

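### The Setswana and English leaflets set different limits on drinking days per week, so the advice given to participants is inconsistent

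*Protocol*

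**What the plan says.** The leaflet is part of the treatment in both arms. Under Brief intervention, the experimental arm receives it with AUDIT feedback and counselling, and step 2 tells the counsellor to "Introduce the sensible drinking leaflet, and emphasise the idea of sensible limits". Under Control arm, participants receive the same Annex 6 leaflet without feedback on their screening result.

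Annex 6 gives two rules for each of three groups.

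- **Setswana, women (Bomme):** "Se nwe go feta dinnotagi tse pedi fela ka letsatsi", then "Se nwe go feta matsatsi a le mabedi mo bekeng".
- **Setswana, men (Borre):** "Se nwe go feta dinno-tagi tse tharo ka letsatsi", then the same day rule as for women.
- **Setswana, over 65:** the same daily limit as for women, then "Se new go feta matsatsi a le mabedi mo bekeng", where two letters of the second word are transposed.
- **English (Appendix 1: Health Education Leaflet English), women:** "No more than 2 drinks per day", then "Do not drink at least 2 days a week".
- **English, men:** "No more than 3 drinks per day", then the same day rule.
- **English, over 65:** the same two rules as for women.

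The Setswana text appears again in two further copies after the English leaflet, with the same day rule each time.

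On language, the protocol says that questionnaires are administered in English or Tswana (Alcohol consumption) and that consent is taken in the participant's preferred language (Adequacy of Protection against Risks). It gives no such rule for the leaflet.

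**The concern.** The two versions should be translations of each other, and on drinks per day they are. On days per week they are not. One limits the number of days on which a person drinks; the other sets a minimum number of days on which a person does not drink. The number two appears in both, which makes the mismatch easy to overlook, but it counts opposite things.

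The leaflet is trial material, and its limits are the ones the counsellor is asked to stress. If the versions are used as printed, two patients of the same sex and age group at the same clinic can be given different advice under the name of one intervention. Anyone describing or repeating the intervention could not tell from the protocol which limit was meant.

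**Working it through.** **Step 1: what the Setswana day rule says, judged from the document itself.** "Se nwe go feta matsatsi a le mabedi mo bekeng" opens with the same four words as the rule above it, "Se nwe go feta dinnotagi tse pedi fela ka letsatsi", whose English counterpart is "No more than 2 drinks per day". The construction is therefore a cap. The protocol's other translations use *go feta* for exceeding a number: the Setswana AUDIT uses it for the top frequency category of item 1 (4 or more times a week), and the Setswana sexual behaviour form uses it for 5 or more partners. The day rule therefore means drinking on no more than two days a week.

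**Step 2: what the English day rule says.** "Do not drink at least 2 days a week" is loosely worded. Its natural reading is that at least two days a week should be free of alcohol. To read it as a two-day cap would need different words.

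**Step 3: permitted drinking days.**

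- Setswana: at most 2.
- English: at most 7 − 2 = 5.

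**Step 4: implied weekly ceiling = drinks per day × permitted drinking days.**

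| Group | Drinks per day (both versions) | Setswana | English | Ratio |
|---|---|---|---|---|
| Women | 2 | 2 × 2 = 4 | 2 × 5 = 10 | 2.5 |
| Men | 3 | 3 × 2 = 6 | 3 × 5 = 15 | 2.5 |
| Over 65 | 2 | 2 × 2 = 4 | 2 × 5 = 10 | 2.5 |

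The ratio is simply 5 days over 2 days. Neither leaflet prints a weekly total, so there is no figure in the plan to reproduce.

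**Step 5: is it a one-off slip?** No. It occurs for all three groups and in every Setswana copy, while the daily limits match throughout. Broken text extraction would not produce that pattern.

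**Step 6: a related mismatch.** The English leaflet gives a tot of spirits as 52 ml at 43%. The AUDIT in Annex 3, the Setswana leaflet and the table headed Alcohol Standard Units give 25 ml at 43%. In pure alcohol this is 52 × 0.43 = 22.36 ml against 25 × 0.43 = 10.75 ml. For spirits, then, the drink being counted also differs between versions.

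**The case against.** The wording mismatch is hard to dispute; the case on the other side is about its consequences, and most of it stands.

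- **A reader might infer that the trial tests two different behavioural targets, so that its effect estimate is a mixture set by the language split.** The documents do not show this. Step 2 asks the counsellor to stress the idea of sensible limits, not to recite the day rule. The session also includes AUDIT feedback, a problem-solving manual, diary cards and a helper, and it follows a counselling manual that is not reproduced in the protocol. Which limit counsellors state, and whether it varies by language, cannot be known from the protocol. Nor does the protocol give a language split or any ground for thinking that the day rule changes the size of the effect.
- **A reader might infer bias between the arms.** This does not follow. The same leaflet goes to both arms, and randomisation balances language between them in expectation.
- **A reader might infer that individual patients receive contradictory advice.** Nothing says that any patient gets both versions. The inconsistency is across patients.
- **Language-matched distribution is itself an inference.** It rests on the existence of two versions and on the language rules for questionnaires and consent.
- **The weekly totals describe advice, not drinking.** AUDIT item 1 would score five drinking days as 4 and two as 3. That is one point on a 40-point scale, it arises only if patients drink exactly at each ceiling, and it could arise in either arm. It is not an effect on the treatment difference.

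None of this removes the contradiction in Annex 6. It limits what may be concluded from it.

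**Conclusion.** The point holds as a fault in the trial material. For women, men and over-65s, the Setswana leaflet allows at most 2 drinking days a week and the English leaflet up to 5, although their drinks-per-day limits agree. The implied ceilings are 4 against 10 drinks a week (women and over-65s) and 6 against 15 (men).

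The conclusion rests on two readings: the Setswana day rule as a cap, which the parallel daily rule supports closely, and the English day rule as a minimum of alcohol-free days, which is its natural sense. That the advice then varies from patient to patient also assumes that each receives the leaflet in their own language.

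What follows is inconsistent intervention content in both arms. It matters more in the experimental arm, where the limits are also stressed in counselling. Bias in the between-arm comparison is not shown.

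**What to change.** Before the leaflet is used, reconcile the day rule between the English leaflet and all the Setswana copies in Annex 6, for all three groups, so that every version states the same limit. Back-translation is one way to do this. Check that the counselling manual and any other session material agree with the reconciled text. Settle the spirit measure (52 ml against 25 ml) across the leaflet versions, the Alcohol Standard Units table and the AUDIT in the same pass. The documents do not show which limit or measure is intended, and this review does not propose one.

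The cost is a text correction, a back-translation check and a reprint. No new form field is needed: item 1.2 of the socio-demographic questionnaire in Annex 1 already records the language spoken most often at home, which is a close proxy for leaflet language if a check by language is wanted.
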